### Oversight and monitoring

#### Data management and storage

Each enrolled participant is assigned a unique study ID. The ID number is linked to each participant’s social security number, stored in a separate coupling key-file in the Services of sensitive data (TSD) at the University of Oslo. TSD uses the highest possible level of IT security, and data files are continuously backed up. Participant self-report data is gathered in BASS (identical security procedures as TSD) and securely exported to TSD for statistical analyses. Trial data are stored at least 5 years after data collection is concluded (anticipated completion date: December 31 st, 2027). A Data Protection Impact Assessment (DPIA) with risk and security measures is in place, collaborating with Sikt (the national agency providing shared digital services and infrastructure for the Norwegian knowledge sector). The Data Protection Official at Sikt and at the Norwegian Centre for Violence and Traumatic Stress Studies (sponsor’s) both acknowledge the DPIA. Only the principal investigators and ERL will have access to the final trial dataset. ANL and EK will have access to the data necessary for the investigation of H6–7. 

#### Safety and monitoring procedures for adverse events

Despite the lack of severe adverse events (AE) in a recent RCT of CIPE [17], the trial has established procedures to monitor AEs and serious adverse events (sAE). Health personnel in the crisis teams are instructed to monitor and address AE continuously. Unmet healthcare needs that are discovered by the research teams in the T1–4 assessments are communicated to the individual’s therapist in the municipality. Moreover, self- and clinician-reported (s)AE are assessed at T2 (see instruments). Adverse events are defined as any unfavorable experience occurring to participants during the trial. Serious adverse events are defined as incidents including death, (attempted) suicide, serious self-harm, acute mania or psychosis, severe intoxication, or other psychological or somatic conditions requiring emergency medical care.

After the first 18 participants are randomized (corresponding to 10% of the target sample size based on the power analysis), an internal pilot study will be conducted in accordance with the CONSORT guidelines for randomized feasibility and pilot trials [77, 78]. The pilot will assess AEs and sAEs. If the rate of AEs is substantially higher than reported in previous studies of CIPE and/or any sAEs occur, the advisory board will consider protocol modifications and/or discontinuation of the trial. Should such deliberations arise, the project owner will retain the final authority to decide whether the trial will be terminated.

### Blinding

The graduate clinical psychology students performing the clinical interviews are blinded. Participants are instructed not to report their assigned condition in interviews. In case of spontaneous unblinding, the interview is terminated and repeated in its entirety by another blinded assessor. Blinding of participants and therapists is not possible due to the nature of the interventions. Data analysis is conducted by the trial statistician (MSB), who is blinded to treatment assignment for the entirety of the trial. ANL and EK perform health economic analyses and are blinded to treatment condition.

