#### Other collected data

A structured adverse events (AE) questionnaire applied in the aforementioned RCT of CIPE [17] is utilized. The questionnaire was used in a previous trial with similar results to face-to-face interviews [69]. The instrument captures the frequency, duration, and nature of possible adverse events, and such events are further classified based on their perceived association with CIPE (related or unrelated). Both participants and clinicians are asked to report and rate participants’ short- and long-term discomfort of any AEs on a scale from 0 (“did not affect me at all”) to 3 (“affected me very negatively”).

In both TAU and CIPE, all time and resource use of therapists (i.e., treatment, travel, online tasks, appointments, preparation, and competence level of therapists) are registered. Registry data is also utilized for all participants, using the Norwegian Patient Register (NPR), Control and Payment of Health Reimbursement (KUHR), Municipal patient- and user-register (KPR), and FD-Trygd. However, in the absence of reliable registry data on the use of health care resources in the municipalities, this study applies survey data reported every second month by the crisis teams’ personnel, via a generic questionnaire. Consultation duration, type (e.g., CIPE, grief support, practical support), and mode (e.g., telephone, video consultation, home visit), as well as the professional background of the involved personnel, are reported from T1 to T4.

In the CIPE + TAU-arm, both clinicians and participants are assessed with a nine-item generic, unvalidated self-report measure of reasons for drop-out from CIPE, in cases where the participant did not finish CIPE. The questionnaire maps lack of motivation, disliking of e-therapy, lack of relevance, lack of reduction of PTSS, worsening of PTSS, remission, concurrent therapy elsewhere, and other (qualitative response category) as possible sources of drop-out. Response is given in one of two categories (0: no, 1: yes), except for the mentioned qualitative item.

Participants are also asked to self-report sociodemographic and background data: year of birth, gender, relationship and cohabitation status, country of birth (self and parents), educational and employment status, current use of psychotropic medication, current psychological treatment (outside of the trial), and ongoing threats or violence.

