### Statistical analyses

H1–3 are tested with linear mixed effects models. The linear mixed effects model includes fixed effects for treatment group (intervention vs. control) and time (post-intervention, 6 and 12 months). In a hierarchical setup, a second step includes a treatment × time interaction. Random effects include random intercepts for participants to account for individual differences. The mixed effects models are applied using the R package nlme [70]. H4–6 are examined using independent t-tests. The quality-of-life change (change in QALY) of participants in CIPE vs. TAU (H6) is analyzed using the mixed effects model. Estimation is conducted using restricted maximum likelihood, with all available observations included, yielding unbiased estimates under the assumptions of missing at random or missing completely at random. For the t-tests, missing data are handled using multiple imputation.

Hypothesis 7 involves a comprehensive economic evaluation comparing the cost-effectiveness of CIPE relative to TAU in terms of both costs and consequences/effectiveness [71]. Costs are assessed using the ingredients approach, which involves three steps: first, identifying each resource required for the intervention; then, measuring these resources; and finally, valuing them. The effectiveness of the intervention is measured by QALY—a composite measure combining both quantity of life (mortality) and quality of life (morbidity) into a single metric [72]. For each arm, mean costs and mean QALYs are estimated across all participants to calculate the incremental cost (ΔC) and incremental effect (ΔQALY). The incremental cost-effectiveness ratio (ICER) or incremental cost per incremental QALY (ΔC/ΔQALY) is then calculated for decision-making. To accept the intervention, ICER should be less than the willingness-to-pay or cost-effectiveness threshold. Since there is no official threshold in Norway, we apply a threshold recommended by the Norwegian Directorate of Health (NOK 500 000 at 2005 prices), adjusted to current price levels [73].

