### Protocol violations and revisions

All included participants are included in the intent-to-treat analyses. Participants who do not complete CIPE within T2, or report adjustment of psychotropic medication or concurrent therapy elsewhere, as well as ongoing traumatization, violence, or threats after T1, and drop out of the trial, are not included in the completers’ analyses. Protocol revisions have been and will be updated in the clinical trial registry and communicated to REK for approval in accordance with the contract.

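### The health economists are described as blinded, but costing CIPE for H7 from records that label CIPE contacts reveals the arm, so the claim cannot cover the cost analysis

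*Protocol article*

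**What the plan says.** All references are to the protocol article.

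- **Blinding.** The health economists "perform health economic analyses and are blinded to treatment condition". The same section says "Data analysis is conducted by the trial statistician", "who is blinded to treatment assignment for the entirety of the trial".
- **Data management and storage.** The economists "will have access to the data necessary for the investigation of H6–7".
- **Other collected data.** Therapist time and resource use, including online tasks, are registered in both arms. Because municipal registry data are judged unreliable, crisis-team staff complete a survey every second month from T1 to T4. It covers "Consultation duration, type (e.g., CIPE, grief support, practical support"), together with mode of contact and professional background.
- **Statistical analyses.** H7 uses the ingredients approach, which starts with "identifying each resource required for the intervention" and goes on to measure and value those resources. Mean costs and mean QALYs are then estimated by arm. A decision model extends the comparison over a lifetime.
- **Protocol violations and revisions.** The completers' analyses leave out, among others, "Participants who do not complete CIPE within T2".

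**The concern.** The blinding statement for the economists is a positive claim of protection against bias, and the article's own data and method defeat it for costs.

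This matters because the economic evaluation leaves the analyst a good deal of judgement: which wider healthcare costs to count, which unit prices to use, what to do about missing contacts, and how to build a model that runs well beyond the trial. If those choices are made with the arm visible while the report says the analysts were blinded, readers will credit a safeguard that did not operate. H7 is a listed hypothesis, and cost-effectiveness is one of the study's three work packages.

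For the statistician the issue is smaller. A blind claimed for the whole trial meets an analysis set whose definition depends partly on an event possible in only one arm.

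**Working it through.** No figure in the plan is at issue and no arithmetic applies. The check sets the statements side by side.

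**Economists, H7 costs**

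1. The economists perform the economic analyses (Blinding) and receive the data needed for H6 and H7 (Data management and storage).
2. The data needed for H7 include municipal resource use. The only source described for this is what therapists and crisis teams report, and the consultation survey has CIPE as a type of contact (Other collected data).
3. CIPE is delivered only in the CIPE + TAU arm (Trial design). A contact coded CIPE therefore works as an arm label for that participant.
4. The ingredients approach cannot avoid this field. To cost CIPE, the analyst must identify its resources, find them in the records and price them (Statistical analyses).
5. A masked A/B code does not help once costs are itemised. The CIPE cost line, which includes therapist time that the Background puts at typically 1 to 3 hours in total, is present in one coded arm and absent in the other.
6. The lifetime model is a model of CIPE specifically, so its inputs must be attached to the right arm.

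Steps 1 to 6 conflict with an unlimited statement that the economists are blinded. The article describes no masking step that would reconcile them.

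**Economists, QALYs**

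EQ-5D-5L and ReQoL-UI scores are self-reported and, as described, carry no CIPE field. A QALY comparison can be run on a masked arm code, so the claim is achievable there.

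**Statistician**

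1. H1–H3 rest on PCL-5, CAPS-5, PHQ-9 and ISI. These can be analysed by intention to treat with coded arms, so the blind is achievable.
2. The completers' rule removes participants for not completing CIPE, and also for reasons possible in either arm: medication change, therapy elsewhere, ongoing threats or violence, and drop-out. Only the first reason is specific to one arm.
3. Applied by the statistician from raw completion data, the rule discloses allocation. Applied by someone else and delivered as a single yes/no flag with coded arms, it need not, although unequal exclusions could still hint at the arm.
4. The article does not say who applies the rule or in what order the analyses are run.

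**The case against.** The strongest reply is that a journal article condenses the full protocol. Arm coding, file release and the point of unblinding commonly sit in the analysis plan or data management plan, which are not shown. The economists are promised only the data they need, and these could be costs already summed per participant. With totals alone, a dearer arm would suggest the allocation without proving it, because TAU itself varies widely (typically 1–4 consultations). The threshold, the NICE-based approach and the planned sensitivity analyses also limit discretion to some degree.

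Part of this stands. That every CIPE participant is identifiable assumes contact-level records reach the economists, which the article does not state outright. But pre-summed costs would move the ingredients costing to someone else, whereas the article gives the economic analyses to the economists. The point is also not a missing detail: the claim as worded has no limit, and an unseen masking procedure would not make it true for itemised costing.

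Three stronger readings are tempting, and the documents do not support them:

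- **The statistician's blind must fail.** It need not, because a flag derived by another person with coded arms could largely preserve it. No stated order of work has the completers' data opened before the primary comparison.
- **The drop-out form used only in the CIPE + TAU arm unmasks the analysts.** The form exists, but no section assigns it to the statistician or the economists, and none of H1–H7 uses it.
- **The access list contradicts the Blinding section.** The list says only the principal investigators and one PhD candidate "will have access to the final trial dataset", and it does not name the statistician as such. Whether the roles overlap cannot be checked from the text, and a coded analysis file is not excluded.

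**Conclusion.** The concern holds for the H7 cost analysis: the economists cannot be blinded to arm while costing CIPE by the method and from the records described. The conclusion assumes that the economists do the ingredients costing themselves, as the Blinding section implies, and that the contact-type field is among the data they receive.

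The reach is limited to the incremental cost, the ICER built on it and the decision model. The size of any bias cannot be estimated from the documents. The QALY comparison can be kept masked. The primary PCL-5 intention-to-treat result at T2 is not affected.

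For the statistician the finding is only that an absolute claim sits beside an analysis set that depends partly on one arm's treatment. The order of work, or who derives the flag, should be fixed. It is not that the blind is already lost.

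**What to change.** 1. **Reword the claim for the economists.** State that the H7 cost analysis is not blind. Keep the blinding claim only for analyses that can run on a masked arm code, such as the QALY comparison.
2. **Fix the discretionary choices first.** Before contact-level records go to the economists, set and date the unit costs, the cost categories included, the handling of missing costs and the structure of the decision model.
3. **Protect the statistician's blind.** Either run H1–H3 on an intention-to-treat file with coded arms before any CIPE-completion data are opened, or have someone else derive the completer flag and name that role.

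The cost is protocol wording and an order of data release, with no new data. Someone outside the blinded analyses must prepare the files, and the article names no such role, so one has to be assigned. The downside is a weaker stated blinding claim for the economic analysis. Recruitment is estimated to finish in September 2026 and the project in December 2027, so the change can be made before the final analyses.

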### Protocol violations and revisions

All included participants are included in the intent-to-treat analyses. Participants who do not complete CIPE within T2, or report adjustment of psychotropic medication or concurrent therapy elsewhere, as well as ongoing traumatization, violence, or threats after T1, and drop out of the trial, are not included in the completers’ analyses. Protocol revisions have been and will be updated in the clinical trial registry and communicated to REK for approval in accordance with the contract.

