### Aims and hypotheses

The study hypotheses and research questions are presented in Table 1. The primary aim is to examine the effectiveness of CIPE, delivered approximately 1 to 2 months after a trauma, as an indicated secondary prevention aimed at reducing PTSS and the incidence of PTSD. We will compare the effect of CIPE + treatment as usual (TAU) vs. TAU only, to examine whether CIPE has the potential to improve the ordinary psychosocial services provided by crisis teams. In such contexts, TAU (see “TAU” under the section “Interventions”) is considered to be an appropriate comparator with several benefits [26, 27]. TAU reflects the current real-world practice of the psychosocial crisis teams against which any added benefit of CIPE must be demonstrated, in order to evaluate if CIPE improves standard care and should be routinely implemented in Norwegian municipalities. The study was designed as an add-on trial (i.e., CIPE as an add-on) due to practical and ethical considerations.

**Table 1 Tab1:** Hypotheses and research questions in the EASE study

Hypotheses concerning the effectiveness and cost-effectiveness of CIPE	
H1	Participants receiving CIPE + TAU will have significantly less PTSS than participants receiving TAU at 6 weeks post T1, and at 6 and 12 months after the traumatic incident
H2	Significantly fewer participants receiving CIPE + TAU will fulfill the criteria for PTSD compared to participants receiving TAU, at 6 and 12 months post trauma
H3	Participants receiving CIPE + TAU will have significantly less symptoms of depression and insomnia than participants receiving TAU at 6 weeks post T1, and at 6 and 12 months after the traumatic incident
H4	Participants in the CIPE + TAU-condition will report significantly higher treatment satisfaction at post-treatment, compared to those in the TAU-condition
H5	Participants with traumatic loss receiving CIPE + TAU will have significantly less symptoms of prolonged grief than participants with traumatic loss receiving TAU 12 months after the loss
H6	Fewer participants in the CIPE + TAU-condition will be referred to second-tier specialty mental health services, and more will achieve improved quality of life within the first year after the traumatic incident, compared to participants in the TAU-condition
H7	The CIPE + TAU implementation is more cost-effective compared to TAU in the short run and may even dominate TAU in the long run (i.e., more effective and less costly)

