### Trial design

The EASE study is a hybrid Type 1 effectiveness and implementation trial [28] (for implementation, see section “implementation trial”). The first part of the study is a parallel two-armed multicenter randomized controlled add-on superiority trial, designed to randomize participants to either CIPE + TAU or TAU only (ratio 1:1). All participants will be offered ordinary crisis team services throughout the trial period. The CIPE group will be given CIPE as an add-on between T1 (4–7 weeks after trauma, dependent on the time of enrollment) and T2 (10–13 weeks after trauma, dependent on the time of T1 [i.e., T2 is always 6 weeks after T1]; see Fig. 1). For those included within 3 weeks from the incident, a screening assessment is performed at the time of recruitment (T0). Baseline assessment and evaluation of inclusion and exclusion criteria will be completed at T1. Outcome measures are gathered 6 weeks post randomization (T1), and follow-up measurements are accomplished at 6- and 12-month post PTE. This trial follows the SPIRIT guidelines and methodology [29] (see Additional file 1 for the SPIRIT checklist).

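### The completers' analysis excludes on post-randomisation events, one of which (CIPE non-completion) can sensibly act in one arm only, so it is open to selection bias of unknown sign; its wording is also ambiguous

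*Protocol article*

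**What the plan says.** All references are to the protocol article.

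- **Protocol violations and revisions** first sets the main population: "All included participants are included in the intent-to-treat analyses". It then defines a second set. Its exclusions start with "Participants who do not complete CIPE within T2, or report adjustment of psychotropic medication or concurrent therapy elsewhere" and end with "ongoing traumatization, violence, or threats after T1, and drop out of the trial, are not included in the completers’ analyses".
- **Trial design** allocates 1:1 to CIPE + TAU or TAU only, so CIPE is offered in one arm. **Randomization** places allocation at T1. Completion of CIPE by T2, and the events after T1, therefore follow allocation.
- **Other collected data** describes a questionnaire on reasons for not finishing CIPE, used in the CIPE + TAU arm only. The listed reasons include "lack of reduction of PTSS, worsening of PTSS, remission, concurrent therapy elsewhere".
- **Aims and hypotheses**, Table 1, H6: "Fewer participants in the CIPE + TAU-condition will be referred to second-tier specialty mental health services".
- **Statistical analyses**, for the mixed models: "Estimation is conducted using restricted maximum likelihood, with all available observations included". The completers' set is not mentioned there, and no hypothesis is tied to it.

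**The concern.** A completers' comparison is usually read as the effect of CIPE among people who took it. Here it would set CIPE completers against a TAU group from which nobody can sensibly be removed for the same reason. TAU participants who would have stopped CIPE, had they been offered it, stay in. If stopping is related to symptoms, the two retained groups differ even when CIPE does nothing.

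The exclusions for other therapy and medication change can apply in both arms, but need not do so equally. If TAU participants with more symptoms seek help elsewhere more often, removing them makes the TAU group look better and shifts the contrast against CIPE.

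The wording is a second problem. The completion criterion is not confined to the CIPE arm, so taken literally it removes every TAU-only participant, because none of them completes CIPE. The chain of conjunctions also leaves open whether each event excludes alone or only together with drop-out. Different readings give different analysis sets, and the choice could be made after the data are seen.

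**Working it through.** The protocol gives no completion rate, no completers' sample size and no completers' power, so there is no figure of its own to reproduce. The only document input is the planning effect, d = 0.3 (Power and sample size calculations). All other inputs below are assumptions, shown as ranges.

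**1. Exclusion for CIPE non-completion only, true effect zero.**
Let Y be the T2 score in SD units (higher is worse). Let a standard normal propensity to complete have correlation -r with Y, and let a proportion c complete. With z the standard normal quantile at 1 - c and φ the standard normal density:

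bias = E(Y | completed) - E(Y in TAU) = -r × φ(z) / c

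For c = 0.70: z = -0.524, φ(z) = 0.348 and φ(z)/c = 0.497. With r = 0.3 the bias is -0.3 × 0.497 = -0.15.

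| Completion c | φ(z)/c | r = 0 | r = 0.2 | r = 0.3 | r = 0.5 | r = -0.3 (remitters stop) |
|---|---|---|---|---|---|---|
| 0.90 | 0.195 | 0 | -0.04 | -0.06 | -0.10 | +0.06 |
| 0.80 | 0.350 | 0 | -0.07 | -0.10 | -0.17 | +0.10 |
| 0.70 | 0.497 | 0 | -0.10 | -0.15 | -0.25 | +0.15 |
| 0.60 | 0.644 | 0 | -0.13 | -0.19 | -0.32 | +0.19 |

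Negative values favour CIPE. A simulation with 1,000,000 per arm agrees to within 0.005.

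**2. Adding exclusion for other therapy or medication change.**
Assume that this removes 10% of CIPE + TAU and 20% of TAU, each correlated 0.3 with a worse score, and that 80% complete CIPE. By simulation the net bias is +0.05 when completion is unrelated to outcome (r = 0), and -0.02, -0.05 and -0.12 for r = 0.2, 0.3 and 0.5. The two selections partly cancel, and the sign depends on the inputs.

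**3. The same with simple proportions.**
Removing a proportion p whose mean is Δ SD worse than those retained lowers the arm mean by p × Δ.
- CIPE non-completers, p = 0.30 and Δ = 0.3 to 0.5: 0.30 × 0.3 = 0.09 and 0.30 × 0.5 = 0.15 SD in favour of CIPE.
- Other therapy, Δ = 0.8, 20% of TAU and 10% of CIPE: 0.20 × 0.8 - 0.10 × 0.8 = 0.08 SD against CIPE.
- Net, ignoring overlap: 0.09 - 0.08 = 0.01 to 0.15 - 0.08 = 0.07 SD in favour of CIPE.

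**4. The two readings of the sentence.**
- Singly: each event excludes on its own, so a participant who starts therapy elsewhere but stays in the trial is removed. Step 2 applies.
- Jointly: events exclude only with drop-out, so that participant stays in. The second selection in steps 2 and 3 then largely disappears.

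**The case against.** The strongest reply is that a completers' set beside intent-to-treat is a common sensitivity analysis, and that its label and estimand may well be settled in an analysis plan not shown here. The same section keeps everyone in the intent-to-treat analyses, the mixed models use all observed data, and no hypothesis rests on the completers' set. This stands, and it sets the severity. It does not remove the point, because the exclusion rule itself is written in the protocol article.

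Three stronger readings are tempting, and the documents do not support them.

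- **That the analysis is biased by construction, or biased towards CIPE.** The drop-out list contains remission, which pushes the other way, and reasons such as low motivation or dislike of online delivery, which need not track symptoms. The r = 0 column shows no bias at any completion rate.
- **That a shift of up to half of d = 0.3 is to be expected.** The 0.15 SD in step 3 is a gross figure under assumed rates. The opposing shift under the same set of assumptions leaves 0.01 to 0.07 SD.
- **That H6 shows that sicker TAU participants will be removed.** H6 concerns referral to specialist services over the first year. The exclusion concerns therapy reported elsewhere. These are different events, nothing in the protocol shows a difference between arms by T2, and on the joint reading those who stay in the trial are not removed at all.

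A complier-average effect also has a price. It assumes that assignment acts only through CIPE exposure. CIPE has four modules with therapist contact, so someone who stops early may still benefit, and binary full completion is therefore a poor exposure. Participants are unblinded, and the section on contamination says that most therapists deliver both conditions, so absence of CIPE exposure in TAU is likely but not guaranteed.

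**Conclusion.** The point holds in a limited form. The completers' contrast compares groups selected after randomisation, by a rule of which one part can sensibly act in one arm only, and the protocol's own drop-out reasons make dependence on outcome plausible. The bias is of unknown sign and size. Over the assumed ranges in step 1 it runs from -0.32 to +0.19 SD, which can be material against d = 0.3, and it is zero if exclusion is unrelated to outcome. These figures rest on assumed completion rates and correlations and on a normal selection model.

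A reader might infer that the primary result is compromised. It is not: the intent-to-treat analyses keep all included participants. Severity is low. The ambiguity of the sentence needs no assumption and should be corrected in any case.

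**What to change.** 1. Replace the completers' comparison, or accompany it, with a complier-average causal effect on PCL-5 at T2. Keep all randomised participants in their allocated arm and use randomised arm as the instrument. Take CIPE started, or number of modules completed, as the exposure, with binary full completion only as a sensitivity analysis. Adjust for T1 PCL-5 and crisis team, and allow for household clustering, since households are randomised together.
2. State the assumptions: assignment has no effect other than through CIPE exposure, and TAU participants have no CIPE exposure. Discuss the second against the reported cases of contamination.
3. Do not exclude participants for other therapy or medication change. Report those rates by arm, together with CIPE non-completion and its reasons.
4. If a completers' analysis is kept, write its criteria separately for each arm, say whether each acts alone or only with drop-out, and label the result supplementary and non-causal.

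**Cost.** A little more analysis work, a wider interval than the completers' comparison would give, and reliance on the exclusion restriction. No new data collection appears necessary: those who do not finish CIPE must already be identified for the drop-out questionnaire, and modules are delivered through the study platform, although the article does not say that module counts are exported. Recruitment is expected to run to September 2026, and the protocol already provides a route for revisions.
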